### Phase 3 main study

2.3

#### Study design and setting

2.3.1

This cross-sectional observational study will be conducted in Guizhou Province, China. This study covers six county-level cities (Guiyang, Zunyi, Liupanshui, Anshun, Bijie, and Tongren) and three autonomous prefectures (Qiandongnan, Qiannan, and Qianxinan). This province is located in southwest China, with a population of over 38 million, of which over 60 years old population is more than 5.93 million. Based on the 2022 data, this region faces several significant challenges compared to China’s overall development, including a notable acceleration in population ageing, a modest level of social development (as evidenced by an urbanisation rate of 54.81%, which is below the national average of 65.20%), and a relatively underdeveloped economy (with a *per capita* GDP of US$ 7,180, representing only 61.03% of China’s average *per capita* GDP).

#### Participants

2.3.2

Consistent with the selection criteria of our pilot study participants.

#### Sampling

2.3.3

LCA model building requires numerous parameters, resulting in a sample size that depends on the necessary model analysis. Therefore, standard sample size calculations cannot comply with LCA requirements. For LCA, some researchers have suggested a minimum sample size of 500 (49), whereas others recommend a minimum sample size ranging from 300 to 1,000 (50, 51); therefore, we plan to recruit at least 4,000 participants. The sample size will satisfy the analytical requirements.

A probability-proportionate-to-size (PPS) sampling method will be used to select participants from Guizhou Province. PPS sampling requires the number of clusters to be not less than 30. In this study, we will assume the selection of 50 groups, with 4,000 people categorised into 50 groups, each containing 80 participants. These 50 groups will be drawn from six county-level cities and three autonomous prefectures. The number of clusters (*n*) in each of six county-level cities and three autonomous prefectures will be calculated as follows: ① The population aged ≥60 years in Guizhou Province (*N*) divided by 50 and ② The number of clusters (*n*) will be equal to the number of integer multiples of n/50 in the corresponding city cumulative population interval. Then, *n* natural villages/streets in the corresponding prefecture-level cities will be randomly selected as *n* clusters relative to the cities. Detailed information on each prefecture-level city cluster is presented in Table 2.

**Table 2 tab2:** Clusters in six county-level cities and three autonomous prefectures.

Township	Population	Accumulative population	*n* of clusters
1.Guiyang	795,475	795,475	7
2.Zunyi	1,126,525	1,922,000	9
3.Liupanshui	409,888	2,331,888	3
4.Anshun	392,951	2,724,839	3
5.Bijie	954,763	3,679,602	8
6.Tongren	579,146	4,258,748	5
7.Qiandongnan	642,509	4,901,257	5
8.Qiannan	585,724	5,486,981	5
9.Qianxinan	443,626	5,930,607	4
Total	*N*	5,930,607	50

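### Table 2 prints a total of 50 clusters but its rows sum to 49 (3,920 people at 80 each), and the rows are not the output of the stated allocation rule

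*Protocol article*

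**What the plan says.** Section 2.3.3 (Sampling) sets a floor on the sample size: "therefore, we plan to recruit at least 4,000 participants". It then gives the cluster structure: "In this study, we will assume the selection of 50 groups, with 4,000 people categorised into 50 groups, each containing 80 participants".

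Clusters are allotted to six cities and three autonomous prefectures in two steps. Step 1 forms an interval: "The population aged ≥60 years in Guizhou Province (*N*) divided by 50". Step 2 makes each area's number of clusters "equal to the number of integer multiples of n/50 in the corresponding city cumulative population interval". That number of villages or streets is then drawn at random within each area.

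Table 2 lists, for each area, the population, the cumulative population and the number of clusters. The cluster column reads 7, 9, 3, 3, 8, 5, 5, 5, 4, and the Total row prints 50.

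**The concern.** The column does not add to its printed total, and the counts do not match what the described procedure would produce. The text sends the reader to Table 2 for the allocation, so the table is a natural working document for drawing clusters. Someone who follows its rows and someone who follows the rule would draw different numbers of clusters in several areas and reach different totals, and the article does not say which governs.

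Because every cluster has the same size, the cluster count sets each area's share of the sample. Section 2.4.4 promises the proportion of older adults in each need class, and those proportions depend on the area shares.

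There is also a symbol error. Step 2 divides n by 50, although n is the cluster count being solved for. Only N, the population in step 1, makes the step workable.

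**Working it through.** **Inputs.** All come from section 2.3.3 and Table 2: the nine populations and cumulative populations, N = 5,930,607, 50 clusters, 80 people per cluster, and a minimum of 4,000.

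**The plan's own figures.** 50 × 80 = 4,000, so the text is consistent with itself. The nine populations sum to 5,930,607 and every cumulative figure reproduces, so the population inputs are sound.

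**Column sum.** 7 + 9 + 3 + 3 + 8 + 5 + 5 + 5 + 4 = 49, not 50. Then 49 × 80 = 3,920; 4,000 − 3,920 = 80; 80/4,000 = 2%.

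**Stated rule.** The interval is I = N/50 = 5,930,607/50 = 118,612.14. Clusters in an area = floor(cumulative population at its upper end / I) − floor(cumulative population at its lower end / I).

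| Area | Population / I | Cumulative / I | Table 2 | Stated rule | Table minus rule |
|---|---|---|---|---|---|
| Guiyang | 6.707 | 6.707 | 7 | 6 | +1 |
| Zunyi | 9.498 | 16.204 | 9 | 10 | −1 |
| Liupanshui | 3.456 | 19.660 | 3 | 3 | 0 |
| Anshun | 3.313 | 22.973 | 3 | 3 | 0 |
| Bijie | 8.049 | 31.022 | 8 | 9 | −1 |
| Tongren | 4.883 | 35.905 | 5 | 4 | +1 |
| Qiandongnan | 5.417 | 41.322 | 5 | 6 | −1 |
| Qiannan | 4.938 | 46.260 | 5 | 5 | 0 |
| Qianxinan | 3.740 | 50.000 | 4 | 4 | 0 |
| Sum | | | 49 | 50 | −1 |

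**Where the printed rows come from.** Rounding each Population / I to the nearest integer reproduces all nine rows. The article does not say that this was done, but the match is complete. Separate rounding need not preserve a total, and here it loses one cluster.

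**Could a random start explain the table?** With a start s between 0 and I, the selection points s, s + I, …, s + 49I all lie within N, so any start gives exactly 50 clusters. A table of 49 cannot result. A scan of starts across the interval gave nine allocations, which differ from Table 2 in 1, 3 or 5 rows. The closest are 7, 9, 4, 3, 8, 5, 5, 5, 4 and 7, 9, 3, 4, 8, 5, 5, 5, 4.

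**Could another interval explain it?** Counting from zero, with intervals from 100,000 to 140,000 in steps of 1, at least two rows always differed.

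**The case against.** The strongest reply is that this is a small table error. The gap is one cluster. The article cites minimum sizes of 500 and of 300 to 1,000 for latent class analysis, and at least 30 clusters for the sampling method; 3,920 people in 49 clusters clear all of these. The 4,000 is not derived from a power or precision target. All of this stands and limits the severity.

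The shortfall is also conditional. The text and the Total row both say 50, and 49 clusters would still reach 4,000 at about 82 people each (4,000/49 = 81.6). So it cannot be said that field teams will in fact survey 3,920 people. The figure holds only if the rows are followed at exactly 80 per cluster.

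The count of five rows assumes no random start. The article states none, and a condensed article might leave one to the full protocol. That qualifies the count of rows but not the contradiction.

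A reader might infer that the table makes the sample less proportionate to population. The figures do not support that: in each of the five differing rows the printed count is nearer the exact quota than the rule's count is (Bijie, 8.049: 8 printed, 9 by the rule).

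Nor is Zunyi alone in losing a cluster. Under the stated rule Bijie and Qiandongnan are also one short. Against exact quotas the largest relative shortfall is in Liupanshui (3/3.456, about −13%), compared with about −5% in Zunyi (9/9.498).

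A misread table is unlikely, since one rounding pattern fits all nine rows.

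**Conclusion.** The inconsistency is established by exact arithmetic. Table 2 allots 49 clusters under a printed total of 50. At the stated 80 per cluster this is 3,920 people, 80 (2%) under the article's own floor. The rows are separately rounded quotas, not the output of the cumulative-interval rule. Counting multiples from zero, Guiyang and Tongren have one cluster too many, and Zunyi, Bijie and Qiandongnan one too few. With a random start, one to five rows differ, and no start gives the printed table.

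The conclusion rests on reading n/50 as N/50 and on the fixed cluster size of 80. It does not extend to the analysis: nothing in the article suggests that 3,920 people would be too few for the latent class model. Nor do text and table name different sets of villages, since these are drawn at random afterwards; only the counts per area differ, by one at most under the rule as written. What is affected is the stated sample size and the claim that the allocation follows the described design. This is a should-fix correction.

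**What to change.** Before clusters are drawn, change n/50 to N/50 in step 2 and reprint the cluster column as 6, 10, 3, 3, 9, 4, 6, 5, 4 (sum 50). This keeps the method as described. It costs one symbol and five table cells, and in the field one cluster that the text already counts. If the full protocol uses a random start, state it and print the column that it produces.

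If the sponsor would rather keep counts close to the exact quotas, replace the rule. Take the whole-number part of each area's population divided by N/50, then give the remaining clusters to the areas with the largest fractional parts. The whole-number parts sum to 45, and the other five clusters go to Qiannan, Tongren, Qianxinan, Guiyang and Zunyi. This gives 7, 10, 3, 3, 8, 5, 5, 5, 4 = 50. Only the Zunyi cell changes, from 9 to 10, but the sentence that describes the method must be rewritten.

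Either way, rule, rows, total and 50 × 80 = 4,000 will agree.

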#### Data collection

2.2.3

Specially trained researchers will work closely with community workers to collect data from the community. First, the researchers will determine the eligible participants according to the inclusion and exclusion criteria through the community health records. The community staff will then contact eligible participants and agree on the investigation time and location based on their initial consent. The place to conduct an investigation is usually the community office or participants’ homes. Subsequently, the two researchers will meet with the participants at an agreed time and place. The researchers will talk to the older adults or their caregivers to explain the purpose of the study and the concept of CBR. Their power includes privacy protection and the termination of investigations at any time. Individuals willing to participate will provide written informed consent before completing the survey. Finally, one of the researchers will send an e-questionnaire QR code prepared in advance to qualified participants. The questionnaire will be completed after the code is scanned using a smartphone. Our researchers will help older people who have difficulty using smartphones complete and submit the questionnaire. After completing the questionnaire, we will pay the participants a particular reward or an equivalent gift (approximately $4–5). Data will be extracted using a questionnaire platform and sorted into Microsoft Excel. The instruments used are as follows:

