#### Interpretation of the results

2.4.4

Once the LCA model is determined, each participant will be assigned to one of the need pattern categories with the highest probability. Through LCA, we will answer our study questions (i) and (ii) and provide a scientific explanation to identify the multiplicity and latent class of rehabilitation needs of older adults in the community and the distribution proportion of each category.

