**Individual characteristics**			
Gender	Older adult’s gender	Categorical	1 = Male, 2 = Female
Age	Older adult’s age	Continuous	Years (roughly divided into 3–4 categories)
Ethnicity	Older adult’s ethnicity	Categorical	1 = Han ethnicity 2 = Other ethnicity
Education level	Current highest level of education	Categorical	1 = Primary education or below 2 = Junior high school 3 = Senior high school 4 = University or college above
Marital status	Current marital status	Categorical	1 = Married 2 = Divorced 3 = Widowed 4 = Never married
Number of children	Number of living children	Categorical	1 = 1 2 = 2 3 = ≥3
Employment status	Employed status in the past year	Categorical	1 = Formal work 2 = Informal work 3 = Retirement
Living resident	Current residence of older adults	Categorical	1 = City community 2 = Urban–rural fringe community 3 = Countryside community
Income groups	Personal income in the past year	Categorical	1 = Low income 2 = Lower middle income 3 = Middle income 4 = Upper middle income 5 = High income
Source of income	Source of the primary income	Categorical	1 = Pension 2 = Work income 3 = Relatives support 4 = Salary 5 = Other
Medical insurance	Medical insurance types	Categorical	1 = Basic Medical Insurance 2 = Commercial Medical Insurance 3 = No Medical Insurance
Having chronic disease	Suffering from chronic diseases	Categorical	1 = Yes 2 = No
Number of chronic diseases	Number of existing chronic diseases	Categorical	1 = 1 kind 2 = 2 or more
Types of chronic diseases	Classification of chronic diseases	Categorical	1 = Respiratory diseases 2 = Cardiovascular diseases 3 = Cerebrovascular diseases 4 = Digestive system diseases 5 = Metabolic diseases 6 = Other

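### Population size allocates clusters to areas but does not govern the draw of villages and streets, so with a fixed 80 people per unit the sample is not PPS at that stage and unweighted class proportions may be biased

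*Protocol article*

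**What the plan says.** Section 2.3.3 (Sampling) of the protocol article names the design: "A probability-proportionate-to-size (PPS) sampling method will be used to select participants from Guizhou Province". The procedure then has three steps.

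- **Clusters per area.** The number of clusters in each of the nine cities and prefectures "will be equal to the number of integer multiples of n/50 in the corresponding city cumulative population interval". The size measure is the population aged 60 or over. Table 2 lists it for the nine areas and for no smaller unit.
- **Units within an area.** "natural villages/streets in the corresponding prefecture-level cities will be randomly selected as" the clusters. No size measure is attached to this draw.
- **People within a unit.** The take is the same everywhere: "with 4,000 people categorised into 50 groups, each containing 80 participants".

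For finding people, section 2.3.4.1 refers back to the pilot study, where "the researchers will determine the eligible participants according to the inclusion and exclusion criteria through the community health records". Section 2.4.4 (Interpretation of the results) says the latent class analysis will give "the distribution proportion of each category". Table 3 lists residence as a possible influence on class, coded "1 = City community 2 = Urban–rural fringe community 3 = Countryside community".

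**The concern.** A fixed take per cluster gives everyone the same chance of selection only when the clusters are themselves drawn in proportion to size. The larger chance of drawing a big unit then offsets the smaller chance of any one person within it. In the article, size is used one level higher, in sharing out clusters among areas, and drops out at the level where it has to offset the fixed 80.

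If the units differ in size, residents of small ones enter the sample too often. The class proportions are a reported result. The article itself treats residence type as a candidate influence on class, so a distorted mix of units could carry through to those proportions and to any pooled level of need. Once the units have been drawn, the selection cannot be undone.

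**Working it through.** **Inputs.** From section 2.3.3 and Table 2: 50 clusters of 80, and nine area totals adding to 5,930,607. Village and street sizes are not given. Two assumptions are needed: that within an area every unit has the same chance (the plain reading of the text), and that the 80 are a random sample of the unit's older adults.

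**The plan's own figure.** 50 × 80 = 4,000, as stated. Reading the printed n/50 as N/50, the interval is 5,930,607 / 50 = 118,612. Counting its multiples in each cumulative interval gives 6, 10, 3, 3, 9, 4, 6, 5, 4, which add to 50. Table 2 prints 7, 9, 3, 3, 8, 5, 5, 5, 4, which add to 49 (49 × 80 = 3,920). Those counts are each area's population divided by the interval and rounded. This is a separate slip to correct. Either set is roughly proportional to population, so the allocation to areas is not the source of the present problem.

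**Inclusion probability.** Let area h have M_h older adults, K_h units and n_h clusters, and let unit i have M_i older adults.

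- Units drawn by PPS: (n_h × M_i / M_h) × (80 / M_i) = 80 n_h / M_h. Unit size cancels. With the Table 2 counts this runs from 3 × 80 / 409,888 = 5.86 per 10,000 (Liupanshui) to 4 × 80 / 443,626 = 7.21 per 10,000 (Qianxinan), around 4,000 / 5,930,607 = 6.74 overall.
- Units drawn at random without regard to size: (n_h / K_h) × (80 / M_i), proportional to 1 / M_i. A person in a unit one tenth the size is ten times as likely to be sampled.

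**Effect on the mix of units.** Suppose streets hold a share s of older adults and are r times the size of villages. Their share of draws is (s/r) / (s/r + 1 − s), which is 1 / (1 + r) when s = 0.5.

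**Effect on a class proportion.** Suppose a class has prevalence 30% in streets and 50% in villages. With s = 0.5 the true figure is 0.5 × 30% + 0.5 × 50% = 40%, and the unweighted bias is (0.5 − street share of draws) × 20 points.

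| Size ratio r (assumed) | Street share of draws | Expected street clusters of 50 | Bias, points |
|---|---|---|---|
| 1 | 50% | 25 | 0 |
| 2 | 33.3% | 16.7 | +3.3 |
| 5 | 16.7% | 8.3 | +6.7 |
| 10 | 9.1% | 4.5 | +8.2 |
| 20 | 4.8% | 2.4 | +9.0 |

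Under PPS the expected share is 50% (25 clusters) in every row.

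**Other street shares.** At s = 54.81% (the article's all-ages urbanisation rate, used only as an illustration) the true figure is 39.0% and the biases at the five ratios are 0, +3.4, +7.1, +8.8 and +9.8 points. At s = 30% they run from 0 to +5.6. If prevalence is the same in both kinds of unit, the bias is zero at every ratio.

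**Precision cost of weighting.** At s = 0.5, relative weights of r (streets) and 1 (villages) multiply the variance by about (1 + r)² / (4r), ignoring clustering and taking the weights as unrelated to the outcome. This gives 1.0, 1.1, 1.8, 3.0 and 5.5 at the five ratios.

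**The case against.** The paragraph opens by announcing PPS, so a random draw of units could have been meant as a size-weighted one, and an article condenses. That stands to this extent: equal probability is the plain reading, not the article's wording. But the same paragraph spells out the size calculation for areas, tabulates sizes for areas only, and then switches to an unqualified random draw. A field team would carry it out as a simple random draw. If PPS was meant, the sentence still needs to say so.

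The allocation to areas is roughly proportional to population. That stands too, and the point is confined to the village and street stage.

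Design weights may sit in an analysis plan that is not shown. Their absence from the article is therefore no part of this point, and bias is conditional on their not being used. Weights would, however, require unit sizes, so those must be available for every unit selected.

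The three research questions concern patterns of need and associated factors, not provincial prevalence, and residence is a listed covariate in the regression. This limits the consequence for the factor analysis. It does not protect the class proportions.

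A reader might go further and infer that small rural villages are over-represented, that some cannot supply 80 people, or that the results would describe villagers instead of the province's older adults. The article gives no village or street size, so it supports only over-representation of small units, whichever those are. Even at the assumed ratio of 20, some street clusters are still expected.

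**Conclusion.** The selection step as written does not deliver PPS at the village and street stage. With 80 people from every unit, inclusion probability varies as 1 / M_i, so people in small units are over-represented in proportion to how much unit sizes differ. That follows from the stated procedure, provided the random draw is read as one without a size measure.

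Whether the class proportions are materially biased is not established. It requires that units differ in size, that class prevalence varies with unit size or type, and that no weights are applied. Under the illustrative assumptions the bias ranges from nil (equal sizes or equal prevalence) through about 3 points at a size ratio of 2 to about 9 or 10 points at a ratio of 20 with streets holding about half of older adults. The ratios, the street shares and the 20-point prevalence gap are assumptions, not figures from the article.

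**What to change.** Amend section 2.3.3 before units are drawn, in one of two ways.

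1. **Preferred.** Within each area, list the villages and streets with their population aged 60 or over, merging any unit too small to supply 80. Draw the area's clusters from the cumulative list with probability proportional to size, then take 80 people at random from the community health records already used to identify eligible people. Unit size then cancels out of the inclusion probability within an area.
2. **If a simple random draw of units is kept.** Record each selected unit's size M_i and the number of units K_h in the area. Weight the class proportions and pooled estimates by the inverse selection probability, K_h × M_i / (80 × n_h).

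The first option costs the work of compiling unit sizes and merging small units. It needs no additional participants. The second also needs unit counts and sizes, and pays in precision: the working suggests little loss if sizes differ twofold and a large one if they differ tenfold or more. The same amendment can correct the Table 2 counts and the printed n/50.

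### Clusters are stratified by area but not by urban-rural type, so the sample's rural share is left to chance and the class proportions lose some avoidable precision

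*Protocol article*

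**What the plan says.** Section 2.3.3 declares probability-proportionate-to-size sampling, "with 4,000 people categorised into 50 groups, each containing 80 participants". On the first stage it says: "These 50 groups will be drawn from six county-level cities and three autonomous prefectures". Table 2 gives each area between 3 clusters (Liupanshui, Anshun) and 9 (Zunyi). For the second stage the text says only that the allotted number of "natural villages/streets in the corresponding prefecture-level cities will be randomly selected". Area is the only stratum named. Neither this section nor the analysis text mentions an urban-rural stratum, a quota or a list ordered by type.

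Elsewhere the protocol treats urban-rural status as relevant:

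- Section 2.3.1 describes the province partly by its urbanisation: "an urbanisation rate of 54.81%, which is below the national average of 65.20" per cent.
- Table 3 in section 2.4.5 includes residence as a possible influencing factor, coded "1 = City community 2 = Urban–rural fringe community 3 = Countryside community".
- Section 2.4.4 makes the proportion of older adults in each class a result of the study.

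**The concern.** Villages and streets differ in the very feature that Table 3 expects may shape rehabilitation needs. If need classes are more common in one type than the other, the estimated class proportions move with the number of clusters that happen to be rural. With 3 to 9 draws per area and nothing controlling the mix, that number is random. Selecting units with probability proportional to size would not change this: the expected rural share would be right, but the realised share would still vary from draw to draw. This component of sampling error can be largely removed before the draw at almost no cost, so the size of the loss decides whether it is worth doing.

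**Working it through.** **The plan's own figures.** 50 × 80 = 4,000 reproduces. The Table 2 counts add to 7 + 9 + 3 + 3 + 8 + 5 + 5 + 5 + 4 = 49, not the printed 50. That is a separate error and has no bearing here: with 49 clusters the standard deviation in step 1 becomes 7.1 instead of 7.0 points.

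**Inputs from the protocol.** 50 clusters of 80; urban share 54.81% (section 2.3.1), so rural share p = 1 − 0.5481 = 0.4519. This is an all-ages provincial figure. The share among people aged 60 or over, and the share in each area, are not given.

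**Assumptions.** Units are otherwise selected correctly in proportion to size; p is the same in every area; overall class prevalence is 30%; the intracluster correlation (ICC) within residence type is 0.02 to 0.05; urban and rural class prevalence differ by d = 5, 10 or 20 points. The protocol gives none of these.

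**Step 1: rural share of the sample.** SD = √[p(1 − p)/50] = √(0.4519 × 0.5481/50) = 0.0704, or 7.0 points. The 95% range is 45.2 ± 1.96 × 7.04, about 31% to 59%. For p between 40% and 60% the SD is 6.9 to 7.1 points, so the all-ages figure is not critical. If areas differ in urbanisation, the area strata already remove a little. With area shares having an SD of 12 points, the SD is √[(0.2477 − 0.0144)/50] = 6.8 points.

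**Step 2: effect on a class proportion.** The variance within residence type is the average of π(1 − π) over the two types, times (1 + 79 × ICC)/4,000. The draw that is not stratified by residence adds p(1 − p)d²/50. Proportional control of residence removes that term, up to rounding of cluster counts.

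Worked case, d = 10 points, ICC = 0.02:

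- Rural prevalence is 0.30 + 0.10 × 0.5481 = 0.3548; urban is 0.30 − 0.10 × 0.4519 = 0.2548.
- Average π(1 − π) = 0.4519 × 0.3548 × 0.6452 + 0.5481 × 0.2548 × 0.7452 = 0.2075.
- Stratified variance = 0.2075 × 2.58/4,000 = 0.000134, SE 1.16 points.
- Added term = 0.2477 × 0.01/50 = 0.0000495. Total 0.000183, SE 1.35 points, which is 17% larger.

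Results for ICC 0.02 to 0.05:

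| Urban-rural gap | SE of added term | SE with residence controlled | SE as planned | Increase |
|---|---|---|---|---|
| 5 points | 0.35 | 1.16-1.61 | 1.21-1.65 | 2-4% |
| 10 points | 0.70 | 1.16-1.60 | 1.35-1.75 | 9-17% |
| 20 points | 1.41 | 1.14-1.57 | 1.81-2.11 | 34-59% |

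Standard errors are in percentage points. The larger percentage in each row belongs to the smaller ICC.

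**The case against.** The strongest reply is that this is a refinement and not an error. The expected rural share is right if units are properly selected, so nothing is biased. The three research questions concern how needs combine, whether similar people have similar needs, and which factors are associated; class proportions are a descriptive result beside them. A rural share anywhere from 31% to 59% still leaves plenty of both types for finding classes and for estimating the residence effect. The size of the loss rests on a gap that no document gives, and at 5 points it nearly vanishes. Part of the loss is ordinary clustering under another name: a 20-point gap alone produces an ICC of about 0.2477 × 0.04/0.21 = 0.047. Finally, the article may condense a full protocol in which the list is ordered. All of this limits how much weight the point can bear. But the article describes the draw step by step, down to cluster counts per area, and the procedure as written has no control of residence.

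Two stronger readings are tempting and should not be drawn.

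- A reader might infer that residence and area become inseparable. An area with 3 draws has a 26% chance (0.4519³ + 0.5481³) of yielding one type only, and the chance of this in at least one of the nine areas is about 63%. But Table 3 contains no area covariate, and even if one were added the other areas would still supply the residence contrast. Those probabilities do not measure a harm.
- A reader might set the 1.41-point component at a 20-point gap against the roughly 0.7 points of simple random sampling with 4,000 people and call it a doubling. The design is clustered, so the right comparator is a clustered design with residence controlled, as in the table.

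**Conclusion.** The point holds as an inexpensive improvement in precision. As written, the draw leaves the rural share to vary with an SD of about 7 points, slightly less if areas differ in urbanisation. The resulting loss in the class proportions is negligible if urban and rural prevalence differ by about 5 points, and material from about 10 points upward. It rests on an assumed gap, an assumed ICC and an all-ages urbanisation figure; only the last has been shown to matter little. It does not invalidate the class solution or the covariate analysis. Whether each village or street is drawn with the right probability is a separate question, which this calculation takes as settled.

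**What to change.** Before the draw, classify every unit on each area's list as street or village, with a written rule for urban-rural fringe units. Within each area, sort the list by type and draw the allotted clusters systematically with probability proportional to the population aged 60 or over. Sorting is preferable to explicit strata because areas with only 3 or 4 clusters cannot be split exactly in proportion. State the procedure in section 2.3.3.

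The cost is the advance classification of units; the numbers of clusters and participants do not change. Some variation from rounding remains in the small areas. Calibrating the class proportions to known urban-rural shares of people aged 60 or over is an optional addition. If the draw has already been made, it is the partial repair that remains, provided those shares are available.
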